## Abstract

The antenatal care is an important service offered to women during pregnancy that aims to guarantee the mother and fetus’s health. In Brazil, although the coverage of this service is high, the outcomes need to be improved. This study aims to implement a pilot study of a group antenatal care among pregnant women in follow up at a Woman´s Hospital of Universidade Estadual de Campinas, a public teaching hospital referral in women’s health. This randomized clinical trial will be conducted. The study group will be composed of a maximum of 15 women that will be followed in a group antenatal care with 11 meetings every 4 weeks or earlier, during all pregnancy period, while control group will receive the individual antenatal care. Sociodemographic data, quality of life, anxiety and depression will be assessed in women from both groups and women’s satisfaction and experience among the intervention group will be evaluated. A 5% significance level was adopted for quantitative analysis and the sample size was calculated based on ambulatory’s flow. A positive result among the intervention group is expected, mainly in providing a better antenatal experience for women and their knowledge of maternal and child health. This study was approved by the Ethics and Research Commission of UNICAMP number of approval: 25333119.2.0000.5404 and the Brazilian Registry of Clinical Trials (REBEC): RBR-8xcjmf UTN code: U1111-1243–6241. Date: jan.2025, version 1.

## Background

The antenatal care is a service with worldwide relevance that offers a follow up of maternal and fetal conditions from pregnancy diagnose to childbirth and happens in one of the three care levels (primary, secondary and tertiary) according to women’s risk [1]. In Brazil, through the Unified Health System (SUS) (a public health system offered to all population), a minimum of 6 individual medical consultations for each woman was established with laboratory and image exams following a protocol according to gestational age and a medical consultation postpartum [2].

A new antenatal care group model is being developed with good outcomes. The main difference compared to the traditional model is the group approach against the individual care. The group antenatal care has been implemented in United States of America [3,4] since 1995 and receives the name of ‘*’Centering Pregnancy*.” In this new model, the care is provided by an obstetric nurse or physician to a group composed by eight to twelve pregnant women with similar gestational age and the group gather from eight to ten times during pregnancy in scheduled meetings with duration to 90–120 minutes.

All provided care are realized at this group environment. The physical evaluation routine, education and woman support with a development of guide discussions about themes related to pregnancy, possible complications, woman and newborn care, contraception and familiar relationship, promoting integral care to these women [1,3–8].

The physical exam is performed separately only by a folding screen, in which the physician auscultates the fetal heartbeat, determines the uterine fundal height measurement and if necessary, a gynecological exam. The physician asks if the woman has any question and request authorization to share the questions with the group. Meanwhile, in the group environment, the pregnant women take turns with the responsibility of evaluating and writing their own weight and blood pressure (using digital device, checked by the medical team) [1,3–8].

The researches have been showing good outcomes to subjective questions about woman experience during group participation, like trend in early breastfeeding, smaller hospitalization rate in Neonatal Intensive Care Unit (NICU) and decrease in preterm labor [4,9]. In women with diabetes, there was a smaller necessity to drug treatment and women who needed insulin used less than half of doses comparing to women that received the traditional care. Preterm labor decreased and an increase in breastfeeding were observed among women with low income and Afro-American and black women, showing that the new model is applicable among different pregnant profiles [5,6,10,11].

The group antenatal care optimizes the health professional routine by reducing the professional’s work time and the need to repeat the information to every patient individually [2,12] and the implementation of this new antenatal care model can attend underlying SUS principles, specialty in relation to comprehensiveness and universality attending.

In Brazil, the coverage of antenatal care in south region achieves 98%, but the quality and maternal-child outcomes need to be improved, and this new strategy shows to be a good alternative to reach greater quality and women’s preparation to the post labor period, promoting better outcomes [7,13,14].

Although group antenatal care with high fidelity to principles in several low- and middle-income settings has shown better perinatal outcomes compared to traditional care [15], more research is needed to describe potential differences in outcomes between group and traditional antenatal care [16].

The current body of literature still supports group antenatal care as a potential tool to decrease racial inequities in antenatal access, quality of care, and maternal mortality. Furthermore, pregnant women can be benefited by participating in the antenatal care group, but more studies are necessary to determine the benefits of this antenatal care approach [1,16].

In Brazil, there are still no studies showing these differences. Therefore, this study aims to: 1) Implement a pilot project of group antenatal care in one of the antenatal care outpatient clinics from the Woman´s Hospital of Universidade Estadual de Campinas (UNICAMP), a public university in Campinas, Brazil; 2) Compare maternal and perinatal outcomes between the women from antenatal group care and the traditional antenatal care; 3) Understand the experience of women followed in antenatal group care and 4) Observe and analyze the meeting’s dynamic of antenatal group care.

## Methods/design

### Study type

Randomized clinical trial.

### Setting

The study will be conducted at the Antenatal Outpatient Clinic of the Center for Comprehensive Care for Women’s Health (CAISM), which is part of the Hospital complex of the Universidade Estadual de Campinas (UNICAMP).

The unit is located in a public Hospital, dedicated to health care, teaching and research. This Hospital is a reference unit for more than 40 municipalities in the region. It offers tertiary hospital care, as well as outpatient care in the areas of gynecology, obstetrics, neonatology and oncology.

The CAISM antenatal outpatient clinic treats pregnant women referred from Primary Health Care who present with gestational risk situations such as: hypertensive disorders, diabetes, thyroid pathologies, obstetric history with complications, among others, or pregnant women with low risk who are divided according to the situation or concomitant disease on different days of the week. The proposed study will begin with the antenatal care that takes place on Thursday, where women with low risk pregnancies are concentrated.

### Inclusion and exclusion criteria

The inclusion criteria are pregnant women with 18 years old or more; gestational age (GA) less than 20 weeks of gestation and antenatal care at the study setting. - The exclusion criteria is professional indication validated by a professor to individualize care (will be sent to the indicated professionals or sectors, e.g., hospitalization, another outpatient clinic, etc.).

### Intervention

Initial training will be provided prior to implementation of the intervention so that all stages are discussed and understood by all members of the delivery team. Topics related to the eleven planned meetings, the needs of women during antenatal and postpartum follow-up, and the references and protocols used for individual and group antenatal models will be discussed. Discussions and training will also be provided on the intervention delivery process and its evaluation, as well as on the characteristics of the interventionists [17]. In addition, an intervention manual was created with the script for each meeting and the materials used in each time allocated to the planned activities.

### Randomization and masking method

After accepting to participate in the research and signing the informed consent form, the researcher will randomly select the assigned group. We will use a computerized randomizer. A random sequence will be generated by a computer software (http://www.random.org/) and will be followed for the allocation of participants into the experimental and control groups. A sealed envelope containing the randomization form previously filled out in the Intervention Group or Control Group, which will be opened and read with the patient.

The study will not be masked, since the pregnant woman and the researcher will know whether the patient belongs to the IG or CG.The Intervention Group (IG) is going to be composed by a maximum of 15 pregnant women. The group will be attending in 11 meetings with approximately two-hour duration each, every 4 weeks or earlier, if necessary, with the following themes discussions:

Nutrition and physical activity during pregnancy; Most common management complaints and signs of complications; Social and social security rights and mental health; Reproductive planning and sexuality; Childbirth preparation guidelines, warning signs and maternity visit; Breastfeeding; Gestational complications and preparation for trousseau; Cognitive and physical development of the child; Nutrition in the fourth quarter; Postpartum follow-up routines and group closure.

### Follow-up

The pregnant women will be followed during all pregnancy period (with one postpartum review) through scheduled visits in every 4 weeks or earlier (according to women necessity), with a minimum of 10 group consultations. The women can come to the hospital other days for laboratory exams, but the attending will always happen in the group.

At each meeting, for each participant, the meeting information will be recorded on an antenatal card, with information like: attendance data, meeting number, gestational age, weight, blood pressure, uterine height, fetal heart rate, fetal movements, fetal presentation, edema, time to return to the clinic, local and professional care. The Control Group (CG) will follow individualized antenatal care according to the service routine, which consists of medical and nursing visits scheduled every 4 weeks or earlier, if necessary.

The data collection process will occur during all antenatal care period. After the inclusion in the research and before starting the antenatal care, the participants (from both groups) will answer a questionnaire about social and demographic questions. Then, will participate in a semi direct individual interview with themes related to women’s expectations about antenatal care and will answer, individually, World Health Organization Quality of Life (WHOQOL brief) [18], State-Trait Anxiety Inventory (IDATE) [19] and Edinburgh [20] scale questionnaires.

Women allocated in intervention group, will participate in focus group also with themes related to women’s expectations about antenatal care, at the first attending of group antenatal care. To evaluate the intervention’s effectiveness, at the finals attending of antenatal care (preferably after 38 weeks of pregnancy) or in postpartum visit, all pregnant women included in the study will answer again the WHOQOL, IDATE and Edinburgh scale questionnaires and a new individual interview will be performed. In all intervention group meetings, pre and post-tests will be carried out on the experience and satisfaction regarding the central theme of each meeting. A new focus group will be performed with both groups (intervention and control).

Women who withdraw or have a medical recommendation to leave IG will be discontinued and these will also participate in an interview with open questions to assess the reasons for giving up on group antenatal care.

Data about pregnancy, maternal and perinatal outcomes will be assessed by medical record review. Strategies like phone call reminder for each appointment and evaluation of women’s satisfaction will be adopted to improve the adherence in study.

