### Ethics approval and consent to participate

The Resolution 466/12 [26] of the National Health Council are being followed. Women with 18 years old or more will be invited to the study and will be included after read, understand and sing the consent form. The researcher will explain the consent form and will inform that they can withdraw the study without any harm or loss in antenatal care. The study data will be used for the sole purpose of this study, and a commitment made to maintain confidentiality as to the identity of the interviewees in the disclosure of the data. This study was approved by the Ethics and Research Commission of UNICAMP under number CAAE: 25333119.2.0000.5404 [S4]. It has also been entered into REBEC: RBR-8xcjmf.

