## Potential limitations and mitigation strategies

The main potential biases of the study are those commonly associated with randomized clinical trials. During the discussions on the study design, several precautions were taken to minimize the risks, as outlined below:

Selection bias: To minimize this risk, we will rely on computer-generated random numbers. Performance bias: To further minimize this, sequentially numbered, opaque, and sealed envelopes will be used. Performance bias: The study will not involve blinding or masking. The authors will discuss potential biases in the process after the completion of the pilot study. Detection bias: There will be no blinding in the outcome assessment, but the authors believe that the outcome cannot be influenced by the lack of blinding.

Some challenges, such as late initiation of prenatal care and the cultural preference for traditional individual prenatal consultations, are anticipated during the recruitment process. To address this, awareness and information about the project will be shared with healthcare professionals to refer women to the project.

Loss to follow-up and participant non-adherence are potential issues, as there may be dropouts or refusals due to the belief that individual consultations are more appropriate, given that this is the traditional model used nationwide. To address this, several strategies will be implemented, including appointment reminders via phone (with patient consent), raising awareness among participants at the end of each session about the importance of the next topic, and reviewing the study objectives at the conclusion of each session.

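### The self-report baseline seems to follow the opening of the allocation envelope, and the statement that lack of blinding cannot influence the outcome is wrong for self-reported scales

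*Protocol article*

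**What the plan says.** **Allocation.** In Randomization and masking method, allocation follows directly on consent: "After accepting to participate in the research and signing the informed consent form, the researcher will randomly select the assigned group". The sealed envelope holds the assignment, "which will be opened and read with the patient". No step is described between signature and envelope. The same section states: "The study will not be masked, since the pregnant woman and the researcher will know whether the patient belongs to the IG or CG".

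**Baseline.** Follow-up places the first assessment thus: "After the inclusion in the research and before starting the antenatal care, the participants (from both groups) will answer a questionnaire". That sentence concerns the sociodemographic questionnaire. The next one adds an individual interview on expectations of antenatal care and the WHOQOL, IDATE and Edinburgh scales.

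**Final assessment.** For effectiveness, late in pregnancy or at the postpartum visit, "all pregnant women included in the study will answer again the WHOQOL, IDATE and Edinburgh scale questionnaires". Procedures and techniques assigns the final interviews and questionnaires to a researcher who took no part in the group.

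**Analysis.** The Statistical analysis section compares groups and time periods by unpaired or paired t-tests or their rank-based counterparts. It names no baseline-adjusted model.

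**Blinding.** In Potential limitations and mitigation strategies, the detection-bias entry concedes that outcome assessment is not blinded, then adds that "the authors believe that the outcome cannot be influenced by the lack of blinding". The performance-bias entry defers discussion until the pilot is complete.

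**The concern.** A baseline measurement should be unaffected by allocation. If a woman learns her arm and then completes an anxiety inventory, a depression scale and a quality-of-life questionnaire, her answers may reflect relief, enthusiasm or disappointment. An expectations interview held at that point may record what she expects of her assigned arm rather than what she expected beforehand. A woman who withdraws on learning her arm would leave no baseline at all.

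A reaction is plausible here because the protocol itself foresees preferences: the limitations section expects a cultural leaning towards individual consultations, and dropouts or refusals for that reason. At stake is how the before/after results are read.

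The detection-bias sentence raises a related but separate problem. Taken at face value, it would let a difference in self-reported scores be presented as free of any influence from knowing the allocation.

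**Working it through.** The protocol gives no figure for this point. The sample size of 12–15 per group rests on recommendations for pilot studies, with no effect size, SD or power, so there is nothing to reproduce. The check is a reading of the sequence, some simple algebra, and one precision calculation.

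**1. Order of steps**

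- Randomization and masking method: consent, then allocation, then an envelope read with the woman.
- Follow-up: baseline comes after inclusion and before antenatal care, from women described as belonging to both groups.
- Ethics approval and consent to participate: women "will be included after read, understand and sing the consent form", so inclusion is tied to consent and not expressly to randomisation.

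Two orders fit this text: consent–envelope–baseline and consent–baseline–envelope. The first is the more natural, because allocation is described as the act that follows consent and the baseline respondents already have groups. The second is not excluded. No passage shown fixes it.

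**2. Which comparisons are exposed**

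Let *d* be the between-arm difference at the final assessment apart from any allocation reaction, *r* the between-arm shift in baseline scores caused by knowing the arm, and *k* the fraction of that shift still present at the final assessment.

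- Difference in change = (*d* + *kr*) − *r* = *d* − (1 − *k*)*r*.
- Difference in final scores = *d* + *kr*. The baseline does not enter.
- Within one arm, the paired change moves by −(1 − *k*) times that arm's own reaction.

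The shift passes in full into change scores only if it has faded by the end (*k* = 0). It cancels there if it persists completely (*k* = 1). If *r* has the same sign as *d*, the change comparison understates the difference; if the opposite sign, it overstates it. Any *kr* remaining in the final scores comes from open-label self-report, and reordering the baseline would not remove it.

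**3. Could the shift be seen in the data?**

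For a difference between two means with *n* per arm, SE = SD × √(2/*n*).

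- *n* = 12: √(2/12) = 0.41 SD.
- *n* = 15: √(2/15) = 0.37 SD.

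Chance alone gives baseline differences within about ±1.96 × SE in 95% of trials: ±0.80 SD at 12 per arm (1.96 × 0.408) and ±0.72 SD at 15 (1.96 × 0.365), treating the SD as known. At a two-sided 5% level (sidedness is not stated, so this is an assumption) and 80% power, the detectable difference by t-test is about 1.20 SD at 12 per arm and 1.06 SD at 15. The normal approximation (1.96 + 0.84) × SE gives 1.14 and 1.02. Bonferroni correction would raise these further. A moderate shift in baseline scores could therefore be neither recognised nor corrected afterwards.

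**4. The detection-bias sentence**

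For quality of life, anxiety and depression the respondent is the assessor, and the protocol says that she is not masked. An outside researcher at the final questionnaires may limit interviewer influence but does not mask the woman answering. The Discussion names these same outcomes as expected benefits of the intervention. The belief therefore fails for them by the protocol's own description.

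**The case against.** The strongest reply is that the order is inferred. A reader might take consent–envelope–baseline to be the written sequence. The documents do not go that far: inclusion is tied to consent, the mention of both groups says who answers and not when the envelope was opened, and the SPIRIT flowchart, where the schedule would normally appear, is not shown. This stands, so baseline scores *may* carry a reaction; it cannot be said that they do. It does not remove the point, because the text permits the unfavourable order and the remedy is the same either way.

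A reader might also infer that all effect estimates are biased, or by a particular amount. Neither is supported. Final-score comparisons do not use the baseline, no baseline-adjusted analysis is named, and the documents give no evidence on size or direction. The protocol expects group care to improve women's experience, yet also expects some women to prefer individual care.

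On blinding, a reader might conclude that the authors deny that it matters at all. They do not: the sentence is a stated belief confined to detection bias, and performance bias is left for later discussion. The belief is also easier to defend for outcomes taken from medical records, such as preterm birth. The criticism is therefore limited to self-reported outcomes, where the outside researcher is a partial safeguard at most.

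**Conclusion.** The point holds in two parts of different strength.

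**Order of baseline and envelope: a cheap improvement.** The natural reading puts the self-report baseline after disclosed allocation, and nothing shown requires it to come first. The possible distortion is confined to paired before/after tests and change-score comparisons. Its size and direction are unknown, and it depends on how far a reaction fades by the final assessment. With a standard error of 0.37–0.41 SD for a baseline difference, a moderate shift would be indistinguishable from chance imbalance. This conclusion rests on an inferred order; a schedule placing baseline before the envelope would settle it.

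**Detection-bias sentence: wrong as written** for quality of life, anxiety and depression, and equally for satisfaction, because unmasked women report these themselves. This part needs no inference about timing.

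**What to change.** 1. In Randomization and masking method and in Follow-up, state that after consent the sociodemographic questionnaire, the expectations interview and the WHOQOL, IDATE and Edinburgh scales are all completed before the envelope is opened. Make the flowchart agree.
2. Replace the detection-bias sentence with one along these lines: quality of life, anxiety, depression and satisfaction are self-reported by women who know their allocation, may be influenced by that knowledge, and will be interpreted accordingly.

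The cost is the order of steps at enrolment and a few sentences of text; sample size, outcomes and care are untouched. One small downside is that baseline data will be collected from some women who then decline their arm, although those women will at least have a baseline. The article reports that recruitment had not started, so on that timeline the change could apply from the first participant.

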### Statistical analysis

The quantitative data will be saved in a spreadsheet of Microsoft Excel® Software and will be stored for a five-year period. A descriptive analysis will be conducted using measures of central tendency and dispersion for quantitative variables and frequencies and percentages for categorical variables. The groups and time periods will be compared with regard to quantitative outcomes using the unpaired or paired Student’s t-test, Mann-Whitney test or paired Wilcoxon test, according to the data distribution.

Data distribution will be assessed using the Shapiro-Wilk test. Pearson’s chi-square, Fisher’s exact or McNemar’s tests will be used for categorical outcomes. The Bonferroni correction [23] will be applied to the significance level according to the number of comparisons made for each outcome variable. The significance level was set at 5% and the program *Statistical Analysis System* (SAS), version 9.4 will be used.

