## Discussion

With the implementation of this intervention, we expect to provide a better antenatal experience for women under our care and thereby meet the WHO and ACOG recommendations for this service [7,8]. We understand the best experience in the sense of being more prepared to manage the pregnancy and postpartum period with greater strengthening for self-care, baby care and empowerment for reproductive choices such as new pregnancies and better contraceptives to be used.

We also expect a positive result in IC related to topics about maternal and child health. Is expected to find a higher quality of life and low rates of anxiety and depression among women in IC when compared with CG. About issues related to child health, is expected low rate of preterm labor, and higher burden among children who mother participates in group antenatal care and a trend in early breastfeeding. With these results, we also believe in an impact on cost reduction [11,14].

Our hypotheses are based in studies developed by Ickovics’ [3,4] in USA, that compared the two models of antenatal care (traditional and in group) and highlighting the benefits of antenatal group care, as: greater knowledge about pregnancy and post labor care, better ability on familiar relationship and more time with the health professionals (about 20 hours against 2 hours in individual attending)

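### The final WHOQOL, IDATE and Edinburgh may be answered before or after birth: this blurs the before-after comparison and would bias the arm comparison if timing differed by arm

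*Protocol article*

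**What the plan says.** Under Follow-up, the repeat questionnaires have a stated purpose: "To evaluate the intervention’s effectiveness". They apply to both arms: "all pregnant women included in the study will answer again the WHOQOL, IDATE and Edinburgh scale questionnaires". They may be given "at the finals attending of antenatal care (preferably after 38 weeks of pregnancy) or in postpartum visit". The 38 weeks is a preference only, the postpartum option has no window, and nothing assigns a woman to one occasion or the other.

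The first set of questionnaires is taken "After the inclusion in the research and before starting the antenatal care", so always in pregnancy, and the eligibility criteria put entry below 20 weeks.

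Under Statistical analysis, groups and time periods are compared "using the unpaired or paired Student’s t-test, Mann-Whitney test or paired Wilcoxon test, according to the data distribution", at a 5% level with a Bonferroni correction. No stratum or term for the occasion of measurement is mentioned.

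The Discussion predicts an effect on these same scales: "Is expected to find a higher quality of life and low rates of anxiety and depression among women in IC when compared with CG". The study is open, and the planned size is 12 to 15 per group.

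**The concern.** Late pregnancy and the period after birth are different states, and there is no reason to expect anxiety, mood and quality of life to be the same in both. Allowing either occasion for one endpoint has two consequences.

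- **Before-after comparison.** The change score is early to late pregnancy for some women and pregnancy to postpartum for others. Its mean depends on how many women fall in each set, even when the arms are balanced.
- **Between-arm comparison.** If more women in one arm are measured postpartum, part of the shift between the two states appears as a treatment effect. Nothing in the article keeps the shares equal, and in an open study the occasion can be settled with the allocation known. The Procedures section has a researcher from outside the group administer the final questionnaires, but that does not fix when they are given.

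With so few women per arm, mixed timing cannot be separated cleanly afterwards.

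**Working it through.** There is no power calculation to reproduce: the 12 to 15 per group rests on recommendations for pilot studies. The shift in scores and the shares measured postpartum are not in the article, so they are assumed and shown as ranges. Scores have unit SD and there is no true arm effect.

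**Spurious arm difference** = (difference in share measured postpartum) × (shift in SD).

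| Gap in share | Shift 0.3 SD | Shift 0.5 SD |
|---|---|---|
| 0 points | 0 | 0 |
| 30 points | 0.3 × 0.3 = 0.09 | 0.3 × 0.5 = 0.15 |
| 50 points | 0.5 × 0.3 = 0.15 | 0.5 × 0.5 = 0.25 |

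**Standard error** of the arm difference at 15 per arm: sqrt(2/15) = 0.365 SD. The bias is thus 0.09/0.365 = 0.25 to 0.25/0.365 = 0.68 standard errors. By normal approximation, a two-sided 5% test then rejects in 5.7% (for 0.25) to 10.5% (for 0.68) of trials, before any Bonferroni correction.

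**Simulation** of the unpaired t-test (20,000 runs, 15 per arm):

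| Women measured postpartum, by arm | Type I error, shift 0.3 SD | Type I error, shift 0.5 SD |
|---|---|---|
| 8 and 8 | 5% | 4% |
| 10 and 4 | 6% | 8% |
| 12 and 3 | 7% | 12% |

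**What the assumed gap needs.** One woman of 15 is 6.7 points, so 30 to 50 points means 4.5 to 7.5 more women measured postpartum in one arm.

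**Noise with equal shares.** A half-and-half mix adds 0.25 × shift² to the variance. For 0.5 SD this is 0.0625, and sqrt(1.0625) = 1.03, so the SD rises by about 3%. For 0.3 SD it is 0.0225, and the SD rises by about 1%.

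**Before-after comparison within one arm** (paired t-test, SD of change taken as 1, no change assumed up to late pregnancy). With 8 of 15 women measured postpartum, the test rejects in 8% (0.3 SD) and 14% (0.5 SD) of runs from the time shift alone. With all 15 postpartum the figures are 19% and 43%. A single fixed time therefore does not remove the natural course from a within-arm test; it makes the change a defined one.

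**Calendar.** Recruitment is planned to end on 30 June 2025 and data collection by January 2026. From 30 June to 31 January is 215 days, or 30.7 weeks. A woman entering on 30 June reaches 38 weeks in that time only if she enters at 38 − 30.7 = 7.3 weeks or later. She reaches six weeks after a 40-week birth (both figures assumed) only if she enters at 46 − 30.7 = 15.3 weeks or later. Which occasion is available thus also depends on entry date and gestational age.

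**The case against.** The strongest reply is that the same rule covers both arms, so the article builds in no difference between them. This stands. With equal shares the bias is zero and the added noise is slight. Even under the assumed gaps, the bias stays below one standard error.

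Two stronger readings are tempting, and neither is supported.

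- **The group's closing meeting falls after birth, so the arms will differ.** The closing theme is "Postpartum follow-up routines and group closure", but it appears in a list of discussion topics without dates, and it can be discussed before delivery. Eleven meetings at four-week intervals would span 10 × 4 = 40 weeks, but the article also allows shorter intervals, and the calendar above leaves at most 39.3 weeks (1 May 2025 to 31 January 2026). The meeting date cannot be inferred. Both arms have last antenatal visits before birth, and the Background describes a postpartum consultation as part of standard public care, so controls have that occasion too.
- **A woman who delivers before 38 weeks can only be measured postpartum, which ties timing to an outcome of treatment.** The 38 weeks is a preference, so an earlier final antenatal reading is allowed. Recruitment also starts in the clinic where low-risk pregnancies are concentrated, and early delivery alone is unlikely to produce a gap of 4.5 to 7.5 women.

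It can also be said that the article is a condensed text, that its SPIRIT figure is not shown, and that a second permitted occasion protects completeness when the authors expect losses to follow-up. A schedule may exist elsewhere, but the published sentence expressly permits both occasions and would still need changing. Completeness is a good reason to keep a fallback, not to pool it unmarked.

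**Conclusion.** The point holds in a limited form. The plan as written pools two states in the scales it uses to judge effectiveness, and the listed tests ignore this. The before-after comparison is affected whatever the balance between arms. The between-arm comparison is exposed to bias if the postpartum shares differ; the article neither prevents that nor shows it to be likely.

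The illustrative size is 0.09 to 0.25 SD against a standard error of 0.37 SD. It rests entirely on an assumed shift of 0.3 to 0.5 SD and an assumed gap of 30 to 50 points. This is modest beside the imprecision of a pilot that detects only about 1.0 to 1.1 SD with 80% power: (1.96 + 0.84) × sqrt(2/n) is 1.02 at n = 15 and 1.14 at n = 12. It is worth correcting because it can be avoided at the design stage and not repaired later.

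**What to change.** - Name one assessment time, with a window, as the analysed endpoint for WHOQOL, IDATE and Edinburgh, the same in both arms.
- Use the other occasion only as a separate secondary time point in all women, or as a flagged fallback that is not pooled in the main comparison.
- Record each assessment date relative to delivery, and report timing by arm.
- Describe within-arm changes as including the natural course from early pregnancy to the chosen time.

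**Cost.** No new instruments are needed, but this is more than a change of wording. Either choice may lose a few women: a late-pregnancy window misses those who deliver before it, and a postpartum window misses those lost to follow-up. If the postpartum visit is chosen, the calendar above shows that late entrants who are early in pregnancy may not reach it by the end of January 2026, so data collection, and the results planned for March 2026, may have to move back.
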